### Sample size

We calculated the sample size based on expected effect size, power, and design effect (intracluster correlation, expected average cluster size [39]).

Sample size was powered to detect small to medium effects in the primary outcome in short-, intermediate and long-term (d = 0.3, 2-sided α = 0.05, 1-β = 0.8). Therefore, 352 persons were required. Furthermore, an intraclass correlation coefficient ICC of 0.02 and an average cluster size of 10 was assumed, resulting in a design effect of 1.18. By multiplication of the design effect and sample size without cluster effect, a necessary sample size of 208 patients in each group was obtained. Overall, we want to include 540 participants, based on an estimated drop-out of about 20%.

Power analyses comprise multiple uncertainties, i.e. ICC, actual cluster sizes, and effect sizes for primary and secondary outcomes. As the magnitude of the ICC varies with the venue of the trial and outcomes, no exact estimation of the ICC was possible because of the lack of data from previous studies reporting on ICC for psychological, behavioral and health outcomes for educational group clusters within inpatient medical rehabilitation. Table 2 shows an overview of possible parameter values (ICC, cluster size). Furthermore, power to detect smaller between-group effects on the secondary outcomes may be too low; thus, effect sizes will be reported throughout. For secondary outcomes, no adjustment for multiple tests is planned.

**Table 2 T2:** Power of analysis of primary endpoint under different assumptions for the design effect

ICC	0.01	0.02	0.05	0.08	0.01	**0.02**	0.05	0.08	0.01	0.02	0.05	0.08
Cluster size	5	5	5	5	10	**10**	10	10	15	15	15	15
Design effect	1.04	1.08	1.20	1.32	1.09	**1.18**	1.45	1.72	1.14	1.28	1.70	2.12
Power (1-β)	0.85	0.84	0.79	0.76	0.83	**0.80**	0.72	0.64	0.81	0.77	0.65	0.55

Bold figures indicate: data for sample size calculation with expected effect size of 0.30 and resulting sample size n = 416.

### Randomization and allocation concealment

Clusters are randomly assigned to the two treatment conditions using a computer-generated list of random numbers. Randomization is performed by a scientific assistant of the research institute (central randomization per phone or e-mail) guarantying allocation concealment until a cluster has been recruited.

HF patients will be recruited at admission to inpatient CR and allocated to the next education group (cluster). Interventions will be performed every two weeks. Randomization results for the clusters will be communicated to the study assistants in each clinic per phone or e-mail only after building of a group and about two days before the intervention starts. Thus, patients will be recruited by physicians masked to later intervention allocation of the respective clusters.

### Blinding

Patients will be blind to the allocated study arm. Educational staff cannot be blinded due to their active role in treatment. Further therapeutic staff of the rehabilitation treatment may be blind to the allocated intervention.

### Statistical methods

All statistical analyses will be performed using SPSS for Windows. Prior to analysis, missing patterns will be explored. Missing data in accordance with missing at random (MAR) assumptions will be imputed using a multiple imputation procedure. Missing values due to drop-out will be analyzed by pair-wise deletion. Non-response-analyses and drop-out-analyses will be carried out by independent group comparisons using *t* tests for continuous variables.

The analysis of the primary and secondary endpoints will be done according to the intention-to-treat principle. Treatment effects (between-group effects) will be evaluated separately for each follow-up time point using multilevel regression analysis [39,40], with treatment group as fixed effects (IG, CG), individuals nested in clusters (education groups) as random effects, and adjusting for baseline values [41]. Statistical significance (p < 0.05, 2-sided) and effect sizes [42] will be reported for all between-group differences. Furthermore, ICCs for primary and secondary outcomes will be reported.

Moderator analysis will be performed by including the moderator variable as an additional fixed factor or covariate and examining interaction effects. Significance levels for interaction effects will not be adjusted due to their exploratory nature.

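### Drop-outs are deleted rather than imputed, so the 6- and 12-month results are available-case estimates that ignore earlier follow-up answers, yet they carry the intention-to-treat label

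*Protocol article*

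**What the plan says.** All the relevant rules are in the protocol article.

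- Statistical methods, on missing data in general: "Missing data in accordance with missing at random (MAR) assumptions will be imputed using a multiple imputation procedure".
- The next sentence, on drop-out: "Missing values due to drop-out will be analyzed by pair-wise deletion".
- The next paragraph, on the principle: "The analysis of the primary and secondary endpoints will be done according to the intention-to-treat principle".
- The same paragraph, on the model: effects are "evaluated separately for each follow-up time point using multilevel regression analysis", with "individuals nested in clusters (education groups) as random effects, and adjusting for baseline values".
- Also in Statistical methods: missing patterns are explored first, and "Non-response-analyses and drop-out-analyses will be carried out by independent group comparisons using" t tests. These steps describe drop-out but do not change the estimate.
- Sample size: "Overall, we want to include 540 participants, based on an estimated drop-out of about 20"%. The primary outcome is powered for the short, intermediate and long term ("d = 0.3, 2-sided α = 0.05, 1-β = 0.8").
- Study design and data collection: the questionnaires are given at admission (t1), discharge (t2), 6 months (t3) and 12 months (t4).

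**The concern.** Drop-out is likely to be the main source of missing data by 12 months, and it is the one source that the plan exempts from imputation. With a separate model per time point and only t1 as covariate, someone who completed t2, or t2 and t3, and then left is absent from the t4 analysis. The answers already given are probably the best available predictors of both the missing score and the decision to leave, and they go unused.

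The 6- and 12-month comparisons are two of the three stated aims. Under this rule they describe the patients who stayed, while the label suggests everyone randomised. If the two arms lose different kinds or numbers of patients, the estimated effect moves away from the effect in all randomised patients.

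**Working it through.** **1. The plan's own figures.** For d = 0.3, two-sided alpha 0.05 and power 0.80, a t-test calculation gives 175.4, so 176 per arm and 352 in total. The design effect is 1 + (10 − 1) × 0.02 = 1.18. Then 176 × 1.18 = 207.7, so 208 per arm and 416 in total. All three stated figures reproduce. Allowing for 20% loss, 416 / 0.80 = 520, so the planned 540 has a margin: 540 × 0.80 = 432 remain, and power is about 0.82 with 432 against 0.80 with 416. Deletion therefore costs no planned power.

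**2. How many patients are left out.** 0.20 × 540 = 108. Deletion acts per time point, so 108 applies only at the visit by which the full 20% has been lost. The article does not say which visit that is. A patient lost after discharge still counts at t2.

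**3. When the contrast is biased.** Let p be the share leaving in an arm, and g the mean outcome of leavers minus that of stayers, in SD units and not explained by baseline. Then

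bias = p(control) × g(control) − p(intervention) × g(intervention).

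The documents give no drop-out pattern by arm, so these gaps are assumptions:
- 20% in each arm, equal gaps: bias 0.
- 20% in each arm, gap −0.3 in the intervention arm and 0 in the control arm: 0 + 0.20 × 0.3 = 0.06 SD.
- 25% intervention against 15% control, gap −0.3 in both: −0.15 × 0.3 + 0.25 × 0.3 = 0.03 SD.

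**4. Simulation of the planned model.** Assumptions: 2,000,000 patients, true effect 0.30 SD at t2 and t4, correlations t1–t2 and t1–t4 of 0.5 and t2–t4 of 0.6, and logistic drop-out on the t2 score calibrated to 20% per arm unless stated. Clustering is ignored. The t4 score is regressed on arm and t1 among completers.

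| Drop-out rises with low t2 score (log-odds per SD) | Planned analysis |
|---|---|
| Intervention arm only, 0.5 / 1.0 | 0.33 / 0.36 |
| Control arm only, 0.5 / 1.0 | 0.27 / 0.24 |
| Same slope and same rate in both arms | 0.30 |
| Intervention 0.5, control 0.25 | 0.32 |
| Intervention 1.0, control 0.5 | 0.32 to 0.33 |
| Slope 0.5 or 1.0 in both arms, 25% intervention against 15% control leaving | 0.32 / 0.33 |

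Arm-specific imputation from t1 and t2 returns 0.30 in every row. A separate run with similar correlations shows that drop-out depending on t1 alone causes no bias, even when it differs by arm. If leaving in the intervention arm depends on the unseen 12-month score itself, deletion gives 0.44 and imputation 0.41.

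**5. Bias against sampling error.** With 432 analysed, SE = sqrt(4 × 1.18 / 432) = 0.105 SD, or about 0.09 after baseline adjustment at correlation 0.5. A bias of 0.06 SD is 0.06 / 0.105 = 0.57 standard errors, which would raise the two-sided type I error from 0.05 to about 0.09.

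**6. Precision.** The planned model already adjusts for t1, so the relevant quantity is the t2–t4 correlation given t1: r = (ρ − 0.25) / 0.75. For ρ = 0.5, 0.6 and 0.7 this gives r = 0.33, 0.47 and 0.60. Effective N = 1 / [(1 − r²)/432 + r²/540] = 442, 452 and 466, a gain of 2% to 8% over 432. This assumes that every drop-out supplied t2.

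**The case against.** Several points on the other side stand.

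- **Intention-to-treat.** A reader might infer a flat contradiction. The article does not define the term, and analysing patients in the arm to which they were randomised is a common reading. On that reading the fault is one of labelling: the analysis is available-case.
- **Certainty of bias.** A reader might infer that deletion is valid only if drop-out is unrelated to outcome given arm and t1. That is too strict for the treatment contrast: drop-out driven by t2 equally in both arms leaves it at 0.30. The article gives no sign of differential drop-out and says patients are blind to their arm. On the other hand, five interactive sessions against one lecture makes some difference in retention conceivable.
- **Size.** The one-arm scenarios are extremes. Milder differences give biases of roughly 0.02 to 0.03 SD, and even 0.06 SD is below one standard error.
- **Reach and power.** A reader might infer that 108 patients are lost to the whole analysis or that the trial becomes underpowered. Neither follows: deletion works per visit, and 432 exceeds 416.
- **Precision.** Using the raw t2–t4 correlation would suggest a larger gain, but t1 is already in the model.
- **Overlapping rules.** Drop-out can itself be missing at random, so the two missing-data sentences overlap, and the article does not say which prevails. The natural reading is that drop-out falls under deletion.

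What remains is a stated rule, not a detail left for a later plan. It discards answers the trial already collects, and the drop-out comparisons do not correct the estimate.

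**Conclusion.** The point holds in a limited form. The stated handling makes the 6- and 12-month effects available-case estimates, excluding up to 108 of 540 patients at the visit by which a 20% loss has occurred. Bias in the contrast requires drop-out linked to the course after baseline, with a pattern or rate that differs by arm. If so, and under the assumed correlations, a true 0.30 SD becomes about 0.32 to 0.36 in one direction and as low as 0.24 in the other; otherwise there is none. The drop-out mechanisms and correlations are assumptions, because the article reports neither. The possible precision gain is small. This should be fixed, but it does not undermine the design.

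**What to change.** Replace the pair-wise deletion sentence. Extend the planned multiple imputation to drop-outs, with arm, education group, t1 and all earlier follow-up scores in the imputation model. An equivalent choice is one multilevel model of t2, t3 and t4 together (occasions within patients within education groups), with the arm effect read off at each time point. Keep the available-case analysis as a sensitivity analysis. If deletion stays primary, describe the results as available-case.

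No new data are needed, only changed wording and a little more programming. The limit is that bias from drop-out depending on unseen outcomes is only partly removed (0.44 falls to 0.41 in the scenario above), so the result would still rest on an untestable assumption. Either approach also implies scores after death, so the new wording should say whether deaths count as drop-out.

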		**Assessment**			
**Outcomes**	**Measures**	**t1**	**t2**	**t3**	**t4**
Self-management competence (primary outcome)	Health education impact questionnaire heiQ, German version [29]. Subscales Self-monitoring and insight, Skill and technique acquisition	X	X	X	X
	Kansas City Cardiomyopathy Questionnaire KCCQ, German version [30]. Subscale self-efficacy	X	X	X	X
Determinants of behavior:					
Intention, action and coping planning, action control	HAPA-scales [31,32]	X	X	X	X
Medication beliefs	Beliefs about Medicine Questionnaire BMQ-D [33], German version	X	X	X	X
Self-management behavior:					
Symptom control	Questionnaire will be developed by our research group	X	---	X	X
Physical activity	Godin Leisure-Time Exercise Questionnaire [34], German modified version	X	---	X	X
Medication adherence	Medication Adherence Report Scale MARS-D, German version [35]	X	---	X	X
Health-related quality of life (disease specific)	Kansas City Cardiomyopathy Questionnaire KCCQ, German version [30]	X	X	X	X
Treatment satisfaction	Short questionnaire developed by our research group [36]	---	X	---	---

t1 indicates admission to rehabilitation; t2, discharge from rehabilitation; t3, 6 months after rehabilitation; t4, 12 months after rehabilitation.

Additionally, sociodemographic parameters (e.g. gender, age, marital status, education, occupation), as well as depression and anxiety (Patient Health Questionnaire, 4 item version PHQ-4 [37]), social support (ENRICHD Social Support Inventory ESSI [38]), smoking, and hospitalization after rehabilitation will be assessed. Medical data (e.g. diagnosis, NYHA, LVEF) will be provided by the attending physician.

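### The primary outcome has three subscales and three follow-ups tested at 0.05, with no lead test or success rule, while the sample size assumes a single 0.05 test

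*Protocol article*

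**What the plan says.** The Objectives section of the protocol article states one superiority hypothesis for the primary outcome, self-reported self-management competence. Table 1 (Outcomes and measurements) lists two heiQ scales for it, "Subscales Self-monitoring and insight, Skill and technique acquisition", and one scale from a second instrument, "Kansas City Cardiomyopathy Questionnaire KCCQ, German version [30]. Subscale self-efficacy". All three are collected at admission (t1), discharge (t2), 6 months (t3) and 12 months (t4).

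Under Statistical methods, "Treatment effects (between-group effects) will be evaluated separately for each follow-up time point using multilevel regression analysis", and "Statistical significance (p < 0.05, 2-sided) and effect sizes [42] will be reported for all between-group differences".

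Under Sample size, "Sample size was powered to detect small to medium effects in the primary outcome in short-, intermediate and long-term", with the parameters "d = 0.3, 2-sided α = 0.05, 1-β = 0.8". "Therefore, 352 persons were required" before clustering, and 208 per group after a design effect of 1.18.

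Multiplicity adjustment is expressly waived for secondary outcomes (Sample size) and for moderator interactions (Statistical methods). Nothing is said about it for the primary outcome.

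**The concern.** One hypothesis is matched to up to nine group comparisons (three subscales at three follow-ups), and the article does not say which of them decides it. The threshold given for every difference is an unadjusted 0.05, and the sample size is calculated for one test at that level.

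This goes beyond detail left to an analysis plan. The article itself fixes the three measures, the separate analysis by time point, the threshold and a single-test sample size, and these do not fit together. If any significant result suffices, the 5% error rate fails. If all three time points are required, the 80% power may fail. What is at stake is what counts as a positive trial: one significant subscale at one visit could be reported as superiority on the primary outcome.

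**Working it through.** **Inputs.** From Sample size: d = 0.3, two-sided α = 0.05, power 0.80, ICC 0.02, cluster size 10, 208 per group, 540 recruited, about 20% drop-out. From Table 1: three subscales and three follow-ups. The article gives no correlations between subscales, between follow-ups or with baseline, so those below are assumptions.

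**1. The plan's own figure.**
- Two-sample t test, d = 0.3, α = 0.05, power 0.80: 175.4, so 176 per arm and 352 in total.
- Design effect: 1 + (10 − 1) × 0.02 = 1.18.
- 176 × 1.18 = 207.7, so 208 per arm and 416 in total.
- Effective size 208/1.18 = 176.3 per arm. Mean z = 0.3 × √(176.3/2) = 2.816, power 0.80.
- 540 × 0.80 = 432, which covers 416.

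The stated figures reproduce, for exactly one test at 0.05.

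**2. Error rate if any significant result counts.** For k independent tests it is 1 − 0.95^k. Correlated cases come from simulated z statistics, with the subscale and time correlations combined as a product.

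| Reading | Independent | Correlations 0.3 | 0.5 | 0.7 |
|---|---|---|---|---|
| Three tests (one score over three times, or three subscales at one time) | 14.3% | 13.6% | 12.5% | 10.9% |
| Nine tests (three subscales × three times) | 37.0% | 34.1% | 29.5% | 22.6% |

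**3. Power if all three time points must be significant, one subscale, d = 0.3 at each.**
- Without baseline adjustment (mean z 2.816): 0.804³ = 0.52 if independent, 0.62 at correlation 0.5 and about 0.66 at 0.7.
- With baseline adjustment, assuming a baseline to follow-up correlation of 0.5 and an unchanged design effect: effective d = 0.3/√(1 − 0.5²) = 0.346, mean z = 0.346 × √(176.3/2) = 3.25, single-test power 0.90. All three: 0.902³ = 0.73 if independent, 0.79 at correlation 0.5, 0.81 at 0.7.

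**4. Power per test if co-equal tests are kept, at the first (Bonferroni) step of Holm, 416 analysed.**

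| Tests | Threshold | No baseline adjustment | Baseline correlation 0.5 |
|---|---|---|---|
| 3 | 0.05/3 = 0.0167 | 0.66 | 0.80 |
| 9 | 0.05/9 = 0.0056 | 0.51 | 0.68 |

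Without baseline adjustment, 0.80 per test at these thresholds would need 233 × 1.18, so 275 per arm and 550 analysed (550/0.80, so 688 recruited) for three tests. For nine it would need 291 × 1.18, so 344 per arm and 688 analysed (860 recruited).

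**The case against.** A reader might infer that the plan prescribes nine separate confirmatory tests, any one of which proves superiority. The article does not say that. Its word for separate analysis applies to time points only. Separate testing of subscales is inferred from Table 1, the lack of a combining rule and the threshold for all differences. The sentence on significance is about reporting, not about a decision rule. This stands, so 23-37% is the figure for one reading only.

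The three time points may also be read as three questions, since the Objectives section names short-, intermediate- and long-term effects as aims. Error control across them is then a choice. That answers only half the point: each question still has three unranked subscales at 0.05, which again gives 11-14%.

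A reader might also infer that the 80% power is plainly not delivered. That is too strong. The sample size statement can mean 80% at each time point, which is correct for one score. The planned baseline adjustment also raises power, provided d = 0.3 is expressed in unadjusted standard deviations. What remains is that 0.80 across all three time points is not assured.

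Finally, multiplicity rules are often left to an analysis plan, which is not shown, and limiting the waiver to secondary outcomes is compatible with separate handling of the primary one. But the article already sets one threshold for all differences and sizes the trial for one test, so the mismatch lies in what it states.

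**Conclusion.** The point holds in this form: the article leaves open which score, which time point and which success rule decide the primary hypothesis, while its stated threshold and its sample size agree only for one named test. The sample size arithmetic is correct for that one test.

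The error rate is about 11-14% on either three-test reading and about 23-37% on the nine-test reading, assuming correlations of 0 to 0.7 and that any significant result counts. Under the opposite rule, all three time points on one subscale, power is about 0.52-0.66 without baseline adjustment and 0.73-0.81 at an assumed baseline correlation of 0.5. The direction of the problem does not depend on these assumptions; its size does.

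**What to change.** Before the data are unblinded, name one primary score and one primary time point, and test that comparison at two-sided 0.05. The score may be one of the existing subscales or a pre-defined combination. This keeps the stated 416 patients and 0.80 power.

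For the remaining primary subscales and time points, either test them afterwards in a pre-stated fixed sequence or by Holm, only if the primary test succeeds, or label them supportive. The order is the sponsor's choice; the article does not rank the subscales or the time points.

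If co-equal primary tests are preferred, use Holm and restate the first-step power: about 0.66 for three tests and 0.51 for nine without baseline adjustment, or 0.80 and 0.68 if a baseline correlation of 0.5 can be justified.

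Cost: a short addition to the analysis wording, and no extra patients under the single-test option. Choosing the score needs a substantive decision, and a combination across two instruments would be a new endpoint needing its own definition. The downside is that a later subscale or time point cannot be claimed as confirmatory if an earlier step fails.

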## Methods/Design

### Study design and data collection

The study is a multicenter cluster randomized controlled trial in four cardiac rehabilitation clinics. Clusters are patient education groups that comprise HF patients recruited within 2 weeks after commencement of inpatient CR. Participants will be recruited consecutively. In the intervention group (IG), patients will receive the new patient-oriented self-management educational program, whereas in the control group (CG), patients will receive a short lecture program (usual care).

Data will be assessed at admission (t1) and three follow-ups, i.e. discharge (t2) and after 6 (t3) and 12 months (t4) using standardized patient questionnaires. Figure 1 shows the study protocol diagram.

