### Participants

Eligibility criteria for participants are a diagnosis of chronic systolic heart failure (ICD-10: I50), left ventricular ejection fraction (LVEF) of 40 or less, and New York Heart Association functional classification (NYHA) of class II or III. Exclusion criteria are acute events of decompensation, cognitive impairment, inadequate German language ability, and severe visual or hearing impairment.

All participants admitted to the rehabilitation clinic during defined time periods (algorithm defined for each clinic) will be eligible for building a cluster (education group), with a minimum of 3 participants per group as a prerequisite.

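### In a four-clinic trial the stated model has no clinic term and the described randomisation no stratification by clinic; the cost is precision and balance, not validity

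*Protocol article*

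**What the plan says.** **Setting.** Study design and data collection: "The study is a multicenter cluster randomized controlled trial in four cardiac rehabilitation clinics". The clusters are patient education groups. Under Participants, the admission periods that define a cluster follow an "algorithm defined for each clinic", so groups are built inside a clinic.

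**Allocation.** Randomization and allocation concealment: "Clusters are randomly assigned to the two treatment conditions using a computer-generated list of random numbers". The process is run centrally by phone or e-mail. Nothing is said about stratifying or blocking by clinic.

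**Model.** Statistical methods gives the terms: "with treatment group as fixed effects (IG, CG), individuals nested in clusters (education groups) as random effects, and adjusting for baseline values". Clinic is absent there, and it is not among the four moderators listed under Objectives.

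**Variance.** Sample size remarks "As the magnitude of the ICC varies with the venue of the trial and outcomes" that no exact estimate was possible. It gives no between-clinic variance.

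**The concern.** The design has three levels (patient, education group, clinic) and the stated model represents two. This is an objection to a model whose terms are written out, so it is more than a detail left for another document.

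Without a clinic term, any difference between clinics in case mix, staff or rehabilitation routine falls into the variance between education groups. What follows depends on how the list was built:

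- **Unstratified list.** Clinics can be unevenly split between arms by chance, and their differences widen the standard error.
- **List stratified by clinic.** The design removes clinic differences from the treatment contrast, but the model still counts them as noise. The standard error is then too large.

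The plan has little room for either loss, since its stated power is 0.80.

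**Working it through.** **1. The plan's own figure.** Inputs from Sample size: "d = 0.3, 2-sided α = 0.05, 1-β = 0.8"; "Therefore, 352 persons were required"; "an intraclass correlation coefficient ICC of 0.02 and an average cluster size of 10 was assumed, resulting in a design effect of 1.18".

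- Two-sample t-test: 175.4, rounded up to 176 per group, 352 in total.
- Design effect: 1 + (10 − 1) × 0.02 = 1.18.
- 176 × 1.18 = 207.7, rounded up to 208 per group, 416 in total. Power is 0.80.

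The stated figures reproduce.

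**2. Chance imbalance, if the list is unstratified.** 540 / 10 = 54 clusters, or 13 to 14 per clinic.

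- Clinic with 14 clusters, split 10:4 or worse: 2 × P(Bin(14, 0.5) ≤ 4) = 2 × 1471/16384 = 0.180.
- Clinic with 13 clusters, split 10:3 or worse: 2 × P(Bin(13, 0.5) ≤ 3) = 2 × 378/8192 = 0.092.
- At least one such clinic among two of 14 and two of 13: 1 − 0.820² × 0.908² ≈ 0.45.

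**3. Loss of precision, by formula.** Let *r* be the clinic share of total variance (assumption, 0 to 0.05), added to a group ICC of 0.02.

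- Clinic ignored: design effect = 1 + 9 × (0.02 + *r*).
- Clinic balanced and modelled: design effect = (1 − 0.02 − *r*) + 10 × 0.02.
- At *r* = 0.02 these are 1.36 and 1.16, so the standard error is √(1.36/1.16) = 1.083 times as large. Power at 416 analysed is 0.746 against 0.811.
- At *r* = 0.01 and 0.05 the standard error ratios are 1.04 and 1.20.

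The second formula assumes clinics exactly balanced between arms and ignores the degrees of freedom spent, so simulation is needed as well.

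**4. Simulation.** 42 groups of 10 (the plan's 416 analysed in groups of 10) in four clinics, true effect 0.30, regression on group means, group ICC 0.02, 10,000 runs per cell (Monte Carlo error about 0.004). Columns give allocation and model; the first four are power.

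| Clinic share | Unstratified, no clinic term | Unstratified, clinic term | Stratified, no clinic term | Stratified, clinic term | Type I error: stratified, no clinic term |
|---|---|---|---|---|---|
| 0 | 0.792 | 0.755 | 0.787 | 0.782 | 0.054 |
| 0.01 | 0.771 | 0.755 | 0.776 | 0.790 | 0.043 |
| 0.02 | 0.744 | 0.768 | 0.750 | 0.791 | 0.037 |
| 0.05 | 0.688 | 0.762 | 0.705 | 0.805 | 0.029 |

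The mean estimate was 0.30 in every cell. Type I error for the unstratified list without a clinic term was 0.050 to 0.054.

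**5. Same check with clinics carrying half of a fixed total ICC** (8,000 runs, columns of power in the same order).

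- Total 0.02: 0.789, 0.775, 0.805, 0.820.
- Total 0.05: 0.709, 0.734, 0.727, 0.771.

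**6. Reading.** Both changes together (first power column to fourth):

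- share 0.01: 0.790 − 0.771 = 0.019
- share 0.02: 0.791 − 0.744 = 0.047
- share 0.05: 0.805 − 0.688 = 0.117
- total ICC 0.02, half from clinics: 0.820 − 0.789 = 0.031

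Clinic term alone after unstratified allocation (first column to second):

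- share 0: −0.037
- share 0.01: −0.016
- share 0.02: +0.024
- share 0.05: +0.074

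**The case against.** The strongest reply is that the planned analysis is already valid. Clusters are randomised, the education-group random effect takes up clinic variance, and chance imbalance is reflected in the standard error. This stands. A reader might infer that clinic differences could pass for a programme effect in the sense of bias or excess false positives. The simulations show neither.

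Three further points also stand, in whole or in part:

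- **The term alone is not a free gain.** Halving the ICC by formula would suggest that a clinic term lifts power from 0.80 to 0.83 at ICC 0.02 and from 0.72 to 0.79 at ICC 0.05. That needs allocation balanced within clinics. After unstratified allocation the simulated changes are 0.789 to 0.775 and 0.709 to 0.734.
- **Some of the variance may already be counted.** If the assumed ICC of 0.02 contains a clinic part, the stated power of 0.80 holds as it is. Table 2 shows power for ICCs up to 0.08, and baseline adjustment may remove part of the clinic case mix.
- **The article is condensed.** Its silence does not show that the list was unstratified; the full protocol may say otherwise. The imbalance figures then fall away. The model does not benefit, because it would be leaving out its own stratification factor.

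The article also does not describe clinic as an established source of variation, nor the ICC as the main uncertainty. It says that the ICC varies with venue and lists the ICC beside cluster sizes and effect sizes.

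**Conclusion.** The point holds as one of precision and balance. The terms are stated, clinic is missing from them, and a better specification is available whichever way the list was built. The planned test is not biased and does not exceed its nominal error rate.

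The size depends on an unknown. For assumed clinic shares of 0.01 to 0.05 of total variance, stratifying and modelling clinic is worth about 2 to 12 power points at the planned sample size. With no clinic variance the difference (0.792 against 0.782) is close to Monte Carlo error. If the list was stratified and the model stays as written, type I error is about 0.03 to 0.04 and power is lost for no benefit.

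These figures assume equal groups of 10, four clinics of similar size, analysis of group means, and no reduction of clinic variance through the baseline covariate.

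**What to change.** 1. State whether the list was stratified by clinic.
2. For clusters not yet allocated, use a separate central list per clinic with varying block sizes. Varying sizes matter because unblinded educational staff know past allocations in their clinic, and a fixed block could reveal the next one to those who recruit.
3. Add clinic as a fixed effect (three indicators) to the primary and secondary outcome models, fixed before outcome data are seen by arm. Four clinics are too few to estimate a clinic variance well as a random effect.

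**Cost.** Three cluster-level degrees of freedom: 40 to 37 with 42 groups, or 52 to 49 with 54. Per-clinic lists add little work because randomisation is already central.

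**If all clusters are already allocated without stratification,** the clinic term is a judgement to make in advance. It gains nothing at a total ICC of 0.02, may cost 3 to 4 power points if clinics do not differ, and gains about 2 points at a clinic share of 0.02 and 7 at 0.05. If allocation was stratified, include the term.
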